### Outcomes

This trial's primary outcome will be the mean change in the CES‐D's total score from baseline to the intervention's scheduled end (5 weeks).^31^ The secondary outcomes are mean changes in total scores of the K6 and the GAD‐7 from baseline to the intervention's end (5 weeks).^46^, ^47^, ^48^, ^49^

### Allocation

Following baseline assessment, participants will be randomly assigned to the experimental group or the waiting‐list control group in a 1:1 ratio. The randomization list will be generated by an independent third party using the blockrand package in R (version 4.5.1) with a replacement block method of appropriate size. To ensure allocation concealment, the block size will not be disclosed until the trial ends. The generated randomization list will be managed at the Central Registration Center at Kagoshima University, and participants will be randomly assigned after completing the baseline questionnaire. These procedures will prevent selection bias.

### Blinding

Due to the intervention's nature, blinding of participants and therapists is not possible, so only evaluators will be blinded. Baseline assessments will be performed before randomization. Additionally, to maintain evaluators' blinding, assessments at 3 and 5 weeks after the intervention begins will be automatically sent to participants via a templated online questionnaire provided by the market research company. Because the trial blinds only evaluators, the need for emergency unblinding is expected to be extremely low.

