## METHODS AND ANALYSIS

### Trial design

This trial is a 5‐week, evaluator‐blinded, 1:1 parallel‐group superiority RCT to determine SPSRS efficacy. It was designed in accordance with the Recommendations for Interventional Trials (SPIRIT) 2025 statement and SPIRIT‐PRO.^37^, ^38^

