#### Center for Epidemiologic Studies Depression Scale

The CES‐D (Japanese version) is a 20‐item self‐report questionnaire that measures depressive symptoms on four subscales: (1) somatic and retarded activity; (2) depressed affect; (3) positive affect; and (4) interpersonal problems.^31^ The CES‐D uses a four‐point Likert scale (A ≤ 1 day, B = 1–2 days, C = 3–4 days, and D = 5–7 days), with each item scored from 0 to 3. Total scores range from 0 to 60, with higher scores indicating more severe depressive symptoms. The CES‐D's reliability and validity have been verified.^31^, ^61^, ^62^, ^63^, ^64^

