To ensure the entered data's accuracy, three researchers will conduct a two‐step verification. First, two researchers will independently enter data into Excel spreadsheets. To verify consistency, the third researcher will then compare the data sent by the research company with the two previously entered datasets. Only the data manager and principal investigator have database access, and they will complete the statistical‐analysis dataset. Changes and updates to these databases will be recorded and monitored using Windows Event Viewer and Excel history functions. In accordance with the principles of role‐based access control, only data managers and principal investigators possess database access rights, and they will finalize the datasets for statistical analysis. At this time, there are no plans to release the datasets to third parties. Furthermore, no secondary analyses are currently scheduled. However, if access to the data is requested for purposes such as secondary analysis or meta‐analysis, it will be granted only after obtaining renewed approval from the ethics review committee (in addition to any third‐party ethics committee) and renewed informed consent from the participants. All this study's obtained information will be stored at Kurashiki Heisei Hospital for 10 years.

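### The trial is labelled evaluator-blinded, but every primary and secondary outcome is self-reported by participants who know their arm

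*Protocol article*

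**What the plan says.** Protocol article, Trial design: "This trial is a 5‐week, evaluator‐blinded, 1:1 parallel‐group superiority RCT to determine SPSRS efficacy". The Methods part of the abstract uses the same label.

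Blinding: participants and therapists cannot be blinded, "so only evaluators will be blinded". The means given for keeping evaluators blinded is that the 3-week and 5-week assessments "will be automatically sent to participants via a templated online questionnaire provided by the market research company". Baseline assessment takes place before randomization.

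Outcomes: the primary outcome is change in CES-D total score to week 5; the secondary outcomes are the corresponding changes in K6 and GAD-7.

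Data collection: the CES-D is a "20‐item self‐report questionnaire that measures depressive symptoms on four subscales". The K6, the GAD-7 and the single-item GRC scale are likewise described as self-report. The section on participant retention says that all outcome assessments are online surveys.

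Discussion: the third limitation admits that expectation or disappointment in the waiting-list group may influence results. The last limitation admits possible performance bias in the intervention's favour because providers and participants are not blinded.

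**The concern.** Evaluator blinding is a claim about who judges the outcome. It tells the reader that, although treatment was open, the measurement was made by someone who did not know the arm. In this trial the measurement is the participant's own answer, and the same section that makes the claim says participants cannot be blinded.

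The label matters because the setting gives knowledge of allocation room to act. The comparator is an overt waiting list. The consent material tells participants that encouraging words are displayed during the videos. The Introduction prefers the CES-D partly because its positive-affect items match a positive-word intervention. A reader who takes the label at face value would credit the between-arm CES-D difference with a protection against biased outcome assessment that the design does not provide.

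**Working it through.** The point rests on the text. The check is to ask, for each measure, who rates it and whether that person can be blinded.

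| Measure | Role (Outcomes; Estimating appropriate intervention time) | Who rates it | Blinded after randomization? |
|---|---|---|---|
| CES-D | primary | participant, online | no |
| K6 | secondary | participant, online | no |
| GAD-7 | secondary | participant, online | no |
| GRC | anchor for the minimal important change, experimental group only | participant, online | no |
| Viewing time | exposure in the ROC analysis, experimental group only | recorded by the system | not an outcome |

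1. Three of three primary and secondary outcomes are rated by participants. The GRC is a fourth self-report measure, but it enters no between-arm comparison.
2. Participants know their arm: one group receives a link, instructions and weekly reminders, and the other is told it may have the intervention after week 5.
3. No interviewer, clinician rater or adjudicator is described. The only mechanism offered is automatic sending, which removes an interviewer's influence but leaves the respondent as rater.
4. Baseline answers precede randomization, so the problem concerns weeks 3 and 5.

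**Figures.** The point disputes no number. The stated sample size reproduces: n = 2(1.960 + 0.842)² / 0.4² = 98.1, so 99 per group by the normal formula. The t-test solution is 99.08, rounded up to 100, and 100 / (1 − 0.5) = 200 per group.

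**Illustration only.** Suppose the true effect is zero and open self-report shifts the mean difference by b SD. The values of b are assumptions; nothing in the documents supports any of them. The chance of a significant result favouring SPSRS is Φ(b·√(n/2) − 1.960):

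| b (assumed) | n = 100 per group | n = 200 per group |
|---|---|---|
| 0.1 | 11% | 17% |
| 0.2 | 29% | 52% |
| 0.3 | 56% | 85% |
| 0.4 | 81% | 98% |

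This shows how the test would respond to a shift of a given size. It does not estimate the size of any shift.

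**The case against.** The strongest reply is that the article is already candid. It says outright that participants cannot be blinded, gives the likely direction of bias and mentions waiting-list expectation. On this view only a term is missing. Much of that stands: the limitations are not silent, and a reader who reaches them is warned. What they do not say is that the outcome assessment itself is unblinded, and the label in the abstract and Trial design still says the opposite.

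A second reply is that evaluators may mean the staff who handle or analyse data. The article does not define the word that way, and the safeguard it offers concerns how questionnaires are sent, not who sees arm codes.

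A reader might go further and infer that the dataset is finalised with knowledge of arm, because the principal investigator manages the viewing-time site and "Only the data manager and principal investigator have database access". The documents do not support this as fact. They do not say whether the outcome database carries arm codes or when viewing time is linked to it. The randomization list is held at the Central Registration Center, and survey data arrive under participant numbers. Details of analyst masking may sit in a fuller document.

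A reader might also infer that the principal investigator alone can stop the trial on sight of the data. Trial stopping rules makes early termination a judgment shared with the Ethics Review Committee, and Data monitoring plans no interim efficacy analysis.

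**Conclusion.** The concern holds as a wrong design label. The trial claims evaluator blinding, but no outcome has an evaluator other than the unblinded participant. This covers all three primary and secondary outcomes and the GRC anchor. It rests on the article's own descriptions of the scales and their online delivery, and on no assumption.

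The size of any resulting bias cannot be derived. The article gives no CES-D standard deviation and no information on reporting shifts. A statement that bias could account for a given share of the 0.4 design effect would rest wholly on assumed values.

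The randomized comparison remains usable as an open-label one. What is wrong is the protection described, together with the absence of a plain statement that outcome assessment is unblinded.

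**What to change.** 1. In the abstract, Trial design and Blinding, replace evaluator-blinded with open-label with participant-reported outcomes. In Blinding, describe automatic sending as a way to standardise administration and avoid interviewer influence.
2. In the limitations, add that outcome assessment is unblinded and that the estimated effect against the waiting list therefore includes expectancy and reporting effects.
3. Optional, if any blinding is still to be claimed: name the masked roles. For example, data cleaning and the primary analysis code could be finalised on dummy arm codes, with viewing-time data linked only afterwards.

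Steps 1 and 2 are wording changes and leave the sample size, outcomes and analysis as they are; the cost is a less favourable design label. Step 3 adds a later file merge and agreement on who holds the arm codes and viewing-time records until then. It would mask the handling of data, but would not make the self-reported outcomes blinded.

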### Data collection

Table 1 shows the outcome assessments' schedule. Information regarding depressive symptoms (primary outcome), psychological distress, and anxiety symptoms will be collected at baseline, 3 and 5 weeks after the intervention begins. Additionally, as a baseline assessment, demographic data will be collected via online questionnaires: gender and age, lifestyle characteristics including sleep duration and exercise, drinking, and smoking habits. To protect users' privacy, the research team will not track the specific video content viewed by participants. Instead, only participants' video‐viewing time will be collected using the SPSRS video‐viewing time recording site managed by the principal investigator. To prevent missing data, the questionnaires are set to reject incomplete responses automatically.

#### Patient Health Questionnaire‐9

The PHQ‐9 (Japanese version) is a 9‐item self‐report questionnaire designed to measure depressive symptoms.^53^ Each item is rated on a scale of 0–3 (0 = not at all, 1 = several days, 2 = more than half the days, and 3 = nearly every day), with a total score from 0 to 24. Higher total scores indicate greater depressive symptoms. Previous studies have validated the PHQ‐9's reliability and validity.^53^, ^54^, ^55^, ^56^, ^57^, ^58^, ^59^, ^60^ Additionally, the PHQ‐9 identifies the presence of MDD.^39^

#### Center for Epidemiologic Studies Depression Scale

The CES‐D (Japanese version) is a 20‐item self‐report questionnaire that measures depressive symptoms on four subscales: (1) somatic and retarded activity; (2) depressed affect; (3) positive affect; and (4) interpersonal problems.^31^ The CES‐D uses a four‐point Likert scale (A ≤ 1 day, B = 1–2 days, C = 3–4 days, and D = 5–7 days), with each item scored from 0 to 3. Total scores range from 0 to 60, with higher scores indicating more severe depressive symptoms. The CES‐D's reliability and validity have been verified.^31^, ^61^, ^62^, ^63^, ^64^

#### Kessler Screening Scale for Psychological Distress

The K‐6 (Japanese version) is a six‐item self‐report questionnaire designed to measure psychological distress.^47^ Each item is rated on a scale of 0–4 (4 = all of the time, 3 = most of the time, 2 = some of the time, 1 = a little of the time, and 0 = none of the time), with a total score from 0 to 24. Higher scores indicate greater psychological distress. Previous studies have confirmed the K‐6's reliability and validity.^47^, ^48^, ^62^, ^63^, ^65^

#### Generalized Anxiety Disorder 7‐item Scale

The GAD‐7 (Japanese version) is a 7‐item self‐report questionnaire designed to measure generalized anxiety disorder.^49^ Each item is rated on a scale of 0 to 3 (0 = not at all sure, 1 = several days, 2 = over half the days, and 3 = nearly every day). The total score ranges from 0 to 21, with higher scores indicating greater anxiety symptoms. Previous studies have investigated the GAD‐7's reliability and validity.^49^, ^54^, ^62^, ^66^, ^67^, ^68^

#### Global Rating of Change Scale

The GRC scales (Japanese version) is a single self‐report measure for assessing subjective well‐being over time.^50^, ^51^ Participants select the most appropriate response from five options (1 = I feel a lot better, 2 = I feel slightly better, 3 = I feel about the same, 4 = I feel slightly worse, and 5 = I feel a lot worse) to the question: “Compared to when we last saw you 5 weeks ago, how have your moods and feelings changed?”

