### Study setting and recruitment timeline

This trial will recruit participants from the panel network (36 million members) of a Japanese market research company (Macromill Group, Tokyo) from October 1, 2025, to March 31, 2030. The research firm will email invitations to panelists aged 18–64, explaining the trial's purpose and procedures. The invitation will include an electronic consent option; individuals who check “consent” will be deemed to have agreed to participate in the main trial and can proceed to the online questionnaire for eligibility assessment. Participants who meet eligibility criteria will then undergo a baseline assessment and be considered enrolled. By the Central Registration Center at Kagoshima University, they will subsequently be randomly assigned to the experimental or the waiting‐list control group. Participants will be scheduled to complete Japanese versions of the CES‐D, Kessler Screening Scale for Psychological Distress (K‐6), and Generalized Anxiety Disorder‐7 (GAD‐7) questionnaires at 3 and 5 weeks after the intervention begins.^31^, ^46^, ^47^, ^48^, ^49^ Additionally, at 5 weeks after the intervention begins, the Global Rating of Change (GRC) scales will be assessed in addition to the CES‐D, K6, and GAD‐7.^50^, ^51^ The CES‐D will be administered during the main trial's eligibility assessment, while the K6 and GAD‐7 will be administered during baseline assessment. At 3 weeks after the intervention begins, assessments will be conducted in the following order: CES‐D, K6, and GAD‐7. At 5 weeks, assessments will be conducted in the following order: CES‐D, K6, GAD‐7, and GRC scales. Demographic information and lifestyle characteristics will be assessed only at baseline. Figure 1 shows the study's flowchart, and Table 1 shows the assessment schedule.

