#### Estimating appropriate intervention time for SPSRS

The estimation of the appropriate SPSRS intervention time will use data from the experimental group. Each participant's reliable change (RC) in depressive symptoms will be defined as a change in the CES‐D score (baseline to 5 weeks) that exceeds the minimal important change (MIC). The appropriate SPSRS video‐viewing time will be estimated by the receiver operator characteristic (ROC) method, which calculates the area under the curve, sensitivity, specificity, and the Youden index.^76^ The maximum Youden index point will be the optimal SPSRS intervention time. A previous study has estimated the CES‐D score's MIC; however, the MIC may vary depending on the disease, the intervention, the follow‐up period, and the estimation method.^77^, ^78^, ^79^ Therefore, the CES‐D score's MIC used as this trial's RC will be estimated using a predictive modeling method anchored to the GRC scales after the experimental group's 5‐week intervention.^78^, ^79^ The ROC method will be implemented with the pROC package, and the predictive modeling method will be conducted with the stats package.

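### The week-5 Global Rating of Change item gives two reference points that differ for anyone who answered the week-3 survey, so the anchor for the CES-D minimal important change is ambiguous (minor)

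*Protocol article*

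**What the plan says.** Under Global Rating of Change Scale, the protocol article describes a single five-option item in its Japanese version and gives the question in English: "Compared to when we last saw you 5 weeks ago, how have your moods and feelings changed".

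Study setting and recruitment timeline fixes when it is asked: "at 5 weeks after the intervention begins, the Global Rating of Change (GRC) scales will be assessed". The same section schedules the CES-D, K6 and GAD-7 "questionnaires at 3 and 5 weeks after the intervention begins", and sets out the intermediate survey separately ("At 3 weeks after the intervention begins, assessments will be conducted in the following order"). The starting CES-D is earlier still: it "will be administered during the main trial's eligibility assessment".

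Estimating appropriate intervention time for SPSRS gives the use of the answer. In the experimental group, a participant counts as reliably changed if the CES-D change between baseline and week 5 is larger than the MIC, and the MIC comes from "a predictive modeling method anchored to the GRC scales". That classification is the outcome in the ROC analysis from which the optimal viewing time is read. The introduction names finding an appropriate intervention duration as the secondary objective and words it as exploration.

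**The concern.** The item treats the last contact and a point five weeks back as the same moment. They would be the same in a design with nothing between baseline and week 5. Here a week-3 survey lies between them, so for anyone who answered it the two phrases name different moments.

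A respondent who follows the last-contact phrase reports change over weeks 3 to 5, and that answer is then paired with a CES-D change over weeks 0 to 5. Someone who improved by week 3 and then stayed level could truthfully report no change despite a large fall in score over the whole period. Such answers loosen the link between anchor and score, and the MIC carries the error into the viewing-time cut-off. According to Blinding and the retention section, the surveys are online and sent automatically, so no assessor is there to explain the question. Once given, an answer does not show which reference point was used.

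**Working it through.** **Interval check.** The inputs are the visit weeks in Study setting and recruitment timeline.

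- Week of the GRC minus week of the preceding scheduled survey: 5 − 3 = 2 weeks.
- Week of the GRC minus start of intervention: 5 − 0 = 5 weeks.
- Interval of the CES-D change paired with the GRC: baseline to week 5, nominally 5 weeks.

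So the number in the item matches the score change. The last-contact phrase matches it only for someone who skipped week 3.

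**Illustration of size.** The plan gives no figure on this point to reproduce: no MIC, no course of improvement over time and no misreading rate. Everything below is assumed, except the analysed number per arm.

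- Mean CES-D improvement over 5 weeks is 5 points, split between weeks 0–3 and weeks 3–5 as in the table.
- The SD of true change is 6 (weeks 0–3) and 4.5 (weeks 3–5). Measurement error SD is 3.5 at each assessment.
- A respondent reports improvement if true change over the interval recalled exceeds a personal threshold with mean 3.5 and SD 1.5.
- A share *f* recalls from week 3, the rest from the start. There are 200,000 simulated participants per cell.
- A logistic model is fitted, logit P(improved) = b0 + b1 × observed 0–5-week change. With *p* the overall share improved, MIC = [logit(*p*) − b0] / b1.

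| Points gained by week 3 + after | f = 0 | f = 5% | f = 10% | f = 25% | f = 50% |
|---|---|---|---|---|---|
| 5 + 0 | 4.0 | 4.2 | 4.5 | 5.1 | 5.8 |
| 4 + 1 | 4.0 | 4.2 | 4.4 | 4.9 | 5.6 |
| 3 + 2 | 4.0 | 4.2 | 4.3 | 4.7 | 5.2 |
| 1 + 4 | 4.0 | 4.0 | 4.1 | 4.2 | 4.4 |
| 0 + 5 | 4.0 | 4.0 | 4.0 | 4.0 | 4.0 |

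The correlation between the anchor and the observed change is 0.65 at *f* = 0 and falls to between 0.47 and 0.51 at *f* = 50%, in every row. So misreading weakens the anchor whatever the time course, but it raises the MIC only when a good part of the gain comes before week 3.

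**Set against sampling noise.** Sample size plans 200 per arm with 50% dropout, so 200 × (1 − 0.5) = 100 analysed. With 100 participants in the same model, the sampling SD of the MIC is about 0.7 points. At 5–10% misreading the shift is at most about 0.5 points, below that noise. At 25% with mostly early improvement it is 0.7 to 1.1 points, as large as the noise or larger, and systematic.

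**The case against.** A reader might infer that the anchor covers the wrong interval for every participant, or that the MIC will be biased upward. The documents support neither.

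- **The item states the right interval.** Five weeks is its only dated reference, and it agrees with the CES-D change. To go wrong, a respondent must set the number aside and follow the last-contact phrase. In an online survey nobody is literally seen at week 3, which makes the number the more natural cue. This stands, and it reduces the point from a wrong interval to an ambiguous one.
- **Not everyone has a week-3 contact.** Someone who misses week 3 but answers week 5 was last assessed at baseline, and for that person the sentence is true. This stands as a matter of wording. In practice the exception may be small in the group that matters: the retention section gives the experimental arm an extra 2300 points for answering the scheduled week-3 and week-5 surveys, and participants who drop out before week 5 never reach the GRC.
- **The administered text is not shown.** Participants answer a Japanese item, and the article gives an English rendering. Whether the Japanese carries the same ambiguity cannot be checked, which limits confidence.
- **Size and direction rest on assumptions.** The misreading share and the time course are not in the documents. With improvement only after week 3, the MIC does not move. This stands in full.
- **Reach is limited.** The MIC uses experimental-arm data and serves an exploratory aim. The primary CES-D comparison, the K6 and GAD-7 comparisons and the sample size do not depend on it.

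What remains is that, for week-3 responders, the item as printed contains two conflicting time cues, and a stated objective rests on the answer.

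**Conclusion.** The point holds as a minor wording fault, with moderate confidence. The intended interval is correct, but the English item also refers to a last contact that, on the trial's own schedule, was 2 weeks earlier for participants who answered week 3. Some could therefore rate the shorter period.

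The likely effect is a weaker anchor and, if much of the improvement occurs by week 3, a higher MIC. Its size is unknown because the misreading share is unknown. On the assumed inputs it runs from nothing to roughly half a point at up to 10% misreading, and to about 1.1 points at 25%. Only the choice of viewing time is exposed. Nothing here bears on the test of efficacy.

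**What to change.** Check the Japanese item as administered. If it carries the same double reference, drop the last-contact phrase and keep one reference point that matches the CES-D change. The opening could read: *Compared with just before you joined this study, about 5 weeks ago*, with the rest of the item unchanged. If the Japanese item already refers only to the start of the study, correcting the English description is enough.

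The cost is one sentence in the online form and a minor ethics amendment, with no extra surveys or participants. The downside is a small departure from the wording used before, and answers collected before the change would be on the old wording. Recruitment is planned to run to March 2030, so an early change would cover most answers.

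Optionally, before the MIC is used, confirm that the GRC correlates more strongly with the 0–5-week than with the 3–5-week CES-D change. Both can be computed from data already planned. This is ordinary anchor checking, and its absence from the article is not a fault.
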